### Retention

Participant retention will be supported through financial compensation for completion of inpatient and 6-month follow-up assessments, provision of transportation, and flexible scheduling including in-home visits when feasible. Participants who discontinue or deviate from the intervention will be encouraged to complete all outcome assessments. Outcome data collected will include neurological measures (ISNCSCI with electromyography), patient-reported outcomes (DN4, SCI Pain Data Set, Neuro-QoL, SCIM), and adverse events to allow continued evaluation of safety and clinical outcomes.

### Data management and monitoring

Clinical data will be collected on protocol-specific electronic Case Report Forms (eCRFs) using UCSF REDCap. Source data will be reviewed regularly by the site Principal Investigators for accuracy and completeness. Research staff will conduct routine checks to ensure timely entry, data integrity, and adherence to the protocol. Electromyography data will be recorded on UCSF/HIPAA compliant laptops and stored in the study specific UCSF Box folder.

Study conduct and participant safety will be monitored continuously by the study team, with immediate reporting of adverse events to the Principal Investigators and regular review of study progress, safety events, and protocol adherence. Adverse events will be recorded, graded, and reported to the UCSF Institutional Review Board and sponsor per regulatory requirements. No formal data monitoring committee is convened given the early-phase design and small sample size; oversight is provided by the investigators. A qualitative interim safety review will be conducted after Phase 1 prior to initiation of Phase 2.

### Analysis of primary and secondary efficacy outcome measures

For all participants, the primary outcome measure(s) will be: incidence of adverse events (number) for Phase 1 and 2 and change in ISNCSCI lower motor score over time for Phase 2. Secondary outcomes in both phases will be: ISNCSCI sensory scores, AIS grade, peak EMG amplitude, and mean EMG amplitude. For Phase I, change scores will be measured between baseline and post-trial, and in Phase II each measure will be taken across 5 trials. For all repeated measures analyses, we will use a factorial within-subjects repeated-measures analysis of variance (RM-ANOVA) to assess statistically significant change over time. This approach will allow us within a single statistical test to assess (1) the overall between-subjects effect of stimulation to determine the group differences between the stimulation and control groups, (2) the difference in changes over time between groups, and (3) the within-subjects effect of stimulation over trials, to determine the extent to which each individual changes over time. The RM-ANOVA procedure will be run for each outcome measure.

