### Intervention and comparator

Transcutaneous spinal stimulation will be delivered using ARC^EX^ device (ONWARD Medical), via skin surface electrodes placed over the spine targeting lumbosacral spinal cord at T10 and L1 using round 3.2 cm in diameter stimulating electrodes, and bilaterally on the iliac crests using rectangular, 7.5 × 13 cm reference electrodes during the intervention. Based on previous studies on safety and efficacy of tSCS, we will use biphasic waveforms with a burst frequency of 30 Hz, a carrier frequency of 10 kHz, with a pulse width of 1,000 μs (Gerasimenko et al., 2015; Keller et al., 2021; Moritz et al., 2024). Stimulation will be delivered continuously for 60 min once (for Phase 1 participants) and once a day for 5 consecutive days (for Phase 2 participants). The intensity of the stimulation will be increased gradually to the motor threshold intensity (Moritz et al., 2024) and lowered until motor responses subside if there are any. Increase in trunk/lower extremity muscle tone will be additionally monitored to assess whether the amplitude of stimulation required to reach motor threshold changes with days post injury + tSCS treatment for Phase 2 participants. If stimulation does not elicit any obvious motor responses due to spinal shock, the stimulation intensity will be chosen based on previously reported ranges of effective stimulation, including those observed in our ongoing clinical trial in patients with chronic low back pain (NCT05265000) which provides ranges of maximum tolerable stimulation intensities in individuals without SCI, who have full sensation. The stimulation parameters used in that study are identical to those proposed in STEP-RAISE, including waveform, pulse width, carrier frequency, and electrode configuration, allowing for adaptation of stimulation intensities if necessary. The specific stimulation parameters and optimal stimulation intensity will be left to the discretion of the investigators during this experimental treatment. A range of the investigated stimulation parameters will be systematically recorded and will be reported as part of the methodology for each participant. The stimulation will be delivered while the participant is lying supine in the ICU bed. The lower motor ISNCSCI exam will be performed within the last 30 min of stimulation to assess whether acute tSCS potentiates volitional lower extremity movement. Although physical therapy (PT) is provided to acute SCI patients, in this trial the goal is to assess whether tSCS alone can be delivered safely, and will not be combined with the standard of care ICU PT. Participants will be continuously monitored and asked to provide any verbal feedback regarding stimulation to ensure there is no pain or discomfort during treatment.

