### Criteria for stopping the intervention

The intervention will be paused for significant hemodynamic changes, defined as a sustained (>15 min) increase or decrease in mean arterial pressure (MAP) of more than 30% from baseline or the last recorded stable value and is clinically symptomatic. It will be stopped if spinal cord perfusion pressure (SCPP) decreases to <65 mmHg for more than 15 min despite standard clinical management, including appropriate vasopressor titration. The intervention will also be paused for severe hemodynamic instability, such as persistent bradycardia, hypotension, or hypertension despite appropriate medical management, or for signs of autonomic dysreflexia, including sudden severe headache, flushing and profuse sweating above the level of injury, hypertension, bradycardia, anxiety, blurred vision, or nausea. Any serious adverse event deemed related to the intervention by the Principal Investigator or the safety monitor, or any unanticipated adverse device effect, will result in immediate suspension of the intervention pending further evaluation. If the patient experiences clinical deterioration that precludes participation (e.g., severe sepsis or coma), the intervention will be paused and reassessed. If the intervention is permanently discontinued, observational data collection will continue without further stimulation or sham trials until hospital discharge.

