### Concomitant and post-trial care

Participation in the study will not alter provision of standard of care during or post-trial. Individuals who consent to participate in the study, will however, have additional experimental assessment and treatment procedures incorporated while they are in ICU. The additional assessments will include blood draws and testing of motor evoked potentials using tSCS. The additional treatment will include a single 60 min of tSCS for Phase 1 participants and 5 days of once daily 60 min of active tSCS or sham tSCS. The frequency of certain standard of care procedures, such as ISNCSCI to assess the neurological status of the participant will be increased to daily assessments. The adherence to intervention protocol will be directly monitored by the research staff who will conduct all experiments during the in-patient hospital stay. Any adverse events related to study procedures will be managed promptly by the clinical team according to institutional standards. Compensation for research-related injury will be provided in accordance with University of California, San Francisco institutional policies. No additional post-trial interventions are planned.

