### Outcomes

Table 1 lists all trial outcome measures and the corresponding abbreviated statistical analysis plan.

**Table 1 tab1:** A list of outcome measures and the corresponding analysis plan.

Outcome measure	Description	Statistical analysis
Primary outcomes (safety)—Phase 1 and 2		
1. Incidence of adverse events (# of observed events/sessions)	Hemodynamic instability Skin irritation Patient condition deterioration Unanticipated adverse events	Data type: Count Data Statistical Test: Fisher’s Exact Test
Primary outcomes (efficacy)—Phase 2		
1. ISNCSCI lower motor scores	Immediate change in scores with acute tSCS Change in scores from baseline to post tSCS	Data Type: Integer Statistical Test: Repeated Measures Analysis of Variance
Secondary outcomes (efficacy)—Phase 1 and 2		
1 ISNCSCI sensory + motor scores	Change in scores from baseline to 7DPI or discharge	Data Type: Integer Statistical Test: Repeated Measures Analysis of Variance
2. Spinally motor evoked potentials (MEPs)	MEP present/elicited (binary measure) (within subject) # of muscles with elicitable MEP	Data Type(s): Binary, Count Statistical Tests: Chi-Square, Fisher’s Exact Test
3. Electromyography (EMG) amplitude	Change in EMG amplitude in the presence of tSCS vs. no stimulation (within subject) Change in number of muscles with EMG output	Data Type(s): Continuous, Count Statistical Tests: Repeated Measures Analysis of Variance, Fisher’s Exact Test
Secondary outcomes (biomarker discovery)—Phase 1 and 2		
1. Neuronal (UCH-L1) and glial cell (GFAP) injury markers in blood	Changes in protein levels from baseline to post tSCS vs. sham	Data Type: Continuous Statistical Tests: Repeated Measures Analysis of Variance
2. CSF proteomics	Changes in protein levels from baseline to post tSCS vs. sham	Data Type: Continuous Statistical Tests: Non-linear Principal Components Analysis, followed by RM-ANOVA on PC scores
Secondary outcomes (patient-reported outcomes)—Phase 1 and 2		
3a. Incidence of neuropathic pain at 6-month follow-up 3b. Severity of neuropathic pain at 6-months follow-up	Modified DN4 questionnaire will be used to assess neuropathic pain at 6-months follow-up in tSCS vs. sham individuals (vs. historical TRACK-SCI participants)	Data Type: Integer, or Binarized at ≤ indicating neuropathic pain Statistical Test: Independent group Student’s *t*-test, or Chi-square

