### Data collection methods

Once consent is obtained, coordinators will record all clinical variables and medical history in a secure, web-based portal (REDCap) in NINDS SCI Common Data Elements format. Within 72–96 h post-injury, patients will undergo baseline assessments including pain questionnaires [DN4 and International Spinal Cord Injury Pain Data Set (ISCIPDS)], International Standards for Neurological Classification of SCI (ISNCSCI) with electromyography (EMG), blood and CSF (if a lumbar drain is already in place for clinical purposes only) sampling for biomarkers. We anticipate that most, if not all, eligible subjects will have a lumbar drain as it is part of standard of care at our institution. Lower motor ISNCSCI will be repeated during the last 30 min of tSCS and at 7 days post-SCI (or at hospital discharge whichever is earlier). Surface EMG recordings obtained during active tSCS may contain stimulation-related artifacts. Appropriate signal processing procedures will be applied prior to analysis to reduce stimulation artifacts as necessary (Kim et al., 2021). Residual artifact contamination will be considered during interpretation of EMG findings.

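### RM-ANOVA across five sessions is a complete-data method for an on-stimulation lower motor score that the protocol's own rules can leave incomplete

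*Protocol article*

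**What the plan says.** **Outcome.** Table 1 (*Outcomes*) gives the Phase 2 primary efficacy outcome, the ISNCSCI lower motor score, two components: "Immediate change in scores with acute tSCS" and "Change in scores from baseline to post tSCS". It assigns repeated-measures ANOVA to both.

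**Timing of the exam.** *Intervention and comparator*: "The lower motor ISNCSCI exam will be performed within the last 30 min of stimulation". *Data collection methods*: "Lower motor ISNCSCI will be repeated during the last 30 min of tSCS and at 7 days post-SCI (or at hospital discharge whichever is earlier". The first exam requires a session; the second does not. *Concomitant and post-trial care* adds that the frequency of ISNCSCI "will be increased to daily assessments".

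**Model.** *Analysis of primary and secondary efficacy outcome measures* says that "in Phase II each measure will be taken across 5 trials" and, for all repeated-measures analyses, "we will use a factorial within-subjects repeated-measures analysis of variance (RM-ANOVA) to assess statistically significant change over time". The procedure is to be run for each outcome measure.

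**Incomplete delivery.** *Criteria for stopping the intervention* lists reasons to pause, stop or suspend. After permanent discontinuation, "observational data collection will continue without further stimulation or sham trials until hospital discharge". The biomarker schedule in *Data collection methods* allows discharge to come before the fifth treatment. *Retention* says that those who discontinue or deviate will be encouraged to complete outcome assessments.

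**The concern.** The on-stimulation score exists only if a session reaches its exam. The repeated factor has five levels, one per session: the stopping criteria also use the word trials for sessions. The article itself foresees participants who will not have all five scores. Classical RM-ANOVA cannot use an incomplete row. Software either refuses the data or drops the participant, including the valid scores from the sessions that were given.

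Two things are at stake for this component. The first is size: a group of 10 has little to spare. The second is composition. Those with incomplete rows may be the ones who became unstable or did not tolerate the session, so what is left is a comparison of people with complete delivery rather than of the groups as randomized. *Sample size* says that the efficacy results will supply variability and effect sizes for later trials, and selective loss would carry into those figures.

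**Working it through.** **Plan's own figures.** The article gives no session-loss rate and no expected number of complete participants, so there is nothing to reproduce on retention. The nearest figure is in *Sample size*: observed power 0.97 for the motor score, eta squared 0.18, in a 60-participant study. With f² = 0.18/0.82 = 0.2195 and noncentrality λ = f² × error df, a within-subject effect gives 0.943 for two time points (df 59) and 0.997 for three (df 118). The number of time points is not stated, so 0.97 can be neither confirmed nor refuted. Nothing below depends on it.

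**Does one missing cell matter?** A simulated dataset of 10 participants × 5 sessions had one cell removed. A standard RM-ANOVA routine (within-subject factor only) rejected it as unbalanced. A mixed model with a random intercept used 49 scores from all 10 participants. Listwise deletion would keep 9 participants and 9 × 5 = 45 scores, discarding 4 valid ones. With the planned 5 per arm, that is 1/5 = 20% of an arm.

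**How many rows would be complete?** Let p be the share of sessions with no exam score. This is an assumption; the documents give no value. Two patterns bound the answer:

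- *Independent losses*: P(all five present) = (1 − p)^5; expected complete = 10(1 − p)^5; P(at least one participant incomplete) = 1 − (1 − p)^50.
- *Losses concentrated in as few people as possible*: 50p sessions lost, five per person, rounded up to whole persons.

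| p | (1 − p)^5 | Complete of 10, independent | P(at least one incomplete), independent | Complete of 10, concentrated |
|---|---|---|---|---|
| 2% | 0.904 | 9.0 | 64% | 9 (1 session, 1 person) |
| 5% | 0.774 | 7.7 | 92% | 9 (2.5 sessions, 1 person) |
| 10% | 0.590 | 5.9 | 99.5% | 9 (5 sessions, 1 person) |
| 20% | 0.328 | 3.3 | over 99.9% | 8 (10 sessions, 2 persons) |

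Permanent discontinuation and discharge cluster within a person, so the independent column overstates the number of rows lost.

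**Effect on precision, as illustration.** Take eta squared 0.18, five sessions, the group-by-time effect, alpha 0.05.

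| Convention | N = 10 | N = 8 | N = 6 |
|---|---|---|---|
| λ = f² × error df, with error df = 4(N − 2) | 0.48 | 0.35 | 0.22 |
| λ = f² × N × 5/(1 − ρ), with ρ = 0.5 assumed | 0.95 | 0.88 | 0.71 |

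The level depends entirely on the convention. The loss from dropping participants appears under both.

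**Which exams survive a missed session?** The 7-day or discharge exam does. The daily ISNCSCI may, but the article does not say whether that exam is off stimulation or is the session exam itself. One timing point bears on this. A first session at 72 to 96 h followed by four more daily sessions puts session 5 at 72 + 96 = 168 h to 96 + 96 = 192 h. The 7-day exam is at 168 h, so for some participants it would come before the last session and not be post-treatment.

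**The case against.** The strongest reply is that deletion is inferred. The article states no complete-case rule and excludes nobody, and missing-data handling commonly sits in an analysis plan that is not shown. That stands: the absence of a missing-data rule is not the point here. What remains is that the article positively names a complete-data method for the primary score. It allows a generalized estimating equation alternative only for the proteomics (*Analysis of biomarker discovery measures*).

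A reader might infer that any stopped or missed session removes the participant from the primary efficacy analysis altogether. The documents do not support this. Several stopping criteria only pause the session, which may resume, and a session stopped after its exam still has a score. The baseline-to-post component does not need every session, and assessments continue after discontinuation.

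A reader might also infer that the loss favours active stimulation, since sham delivers no current and stops caused by current can arise only in the active arm. That direction is possible but not shown. The haemodynamic, perfusion-pressure and deterioration criteria apply to both arms, and losing unstable sham participants would work the other way. Early discharge may remove people who are doing well. It also need not be common: the background section gives an average initial stay of 11 days, and session 5 falls at about day 7 to 8.

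Finally, *Sample size* calls the efficacy analyses exploratory. That lowers the stakes, but those same estimates are meant to inform later trials.

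**Conclusion.** The point holds for the on-stimulation component of the Phase 2 primary lower motor score. The article fixes RM-ANOVA across five sessions for a score that its own stopping and discharge provisions can leave missing. By default, one missing session score costs up to four valid ones and 20% of an arm of five. Under assumed session losses of 2% to 20%, complete rows would number about 9 of 10 in the mildest case. In the heaviest they would number between 3.3 (independent losses) and 8 (concentrated losses). These figures rest on assumed rates and on the default behaviour of the method, not on anything the article states about exclusions.

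The point does not extend to the baseline-to-post component as an outcome, and no direction of bias is established. It should be changed, but no confirmatory conclusion depends on it.

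**What to change.** In *Analysis of primary and secondary efficacy outcome measures* and in Table 1, replace RM-ANOVA for the lower motor score with a linear mixed model. It should have arm, session or day, and their interaction as fixed effects; a simple covariance structure such as a random intercept, given 10 participants; REML estimation; and Kenward-Roger degrees of freedom. Use all available scores from all randomized participants, analysed as randomized.

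Analyse the two components separately:

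- *Immediate on-stimulation change*: delivered sessions only, with the number of missing session scores reported by arm.
- *Baseline to post*: the already planned daily and 7-day or discharge exams, used whether or not that day's session was given.

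For the second component, the article should say whether the daily ISNCSCI is off stimulation and separate from the session exam, and should reconcile the 7-day exam with the timing of session 5.

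The model change costs only wording. If the daily exam turns out to be the session exam, using it off stimulation would mean an extra exam on treatment days. The mixed model assumes that scores are missing at random given the observed ones, which tolerance-related stops may violate. That is still a weaker assumption than the one behind complete-case RM-ANOVA. The model also cannot supply on-stimulation scores for someone who never has a session exam, which is why the counts by arm are needed.

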For ISNCSCI and neurophysiological assessment, the participant will be instrumented with 10 surface electromyography recording electrodes (Delsys, Inc), placed bilaterally over the lower extremity muscles: Rectus Femoris (RF), Biceps Femoris (BF), Medial Gastrocnemius (MG), Tibialis Anterior (TA), Extensor Hallucis Longus (EHL). Stimulating electrodes will be placed on the skin over the low thoracic, lumbar spine and the grounding electrodes will be placed over the iliac crest bilaterally. The stimulation will be delivered as single, 1-ms monophasic square-wave pulses every 6 s while patient is lying in supine. Using 2-mA increments, the stimulation intensity will be increased from 2 to 100 mA or if the participant requests to stop stimulation. Three stimuli will be delivered at each intensity. The stimulation will be delivered using an experimental Neo-Stim 5 (Cosyma, LTD) transcutaneous spinal cord stimulator, as ARC-Ex currently does not support single-pulse tSCS paradigm required to evoked discrete motor responses. Neurophysiological outcome measures will include the presence or absence of elicitable motor evoked potentials (MEPs) and the number of muscles demonstrating elicitable responses (Table 1). The neurophysiological assessment will be performed at baseline twice (before and right after the first 60 min of continuous tSCS) and at 7 days post-SCI (or at hospital discharge whichever is earlier) if the standard of care continuous vital signs monitoring is still ongoing. Frequent vital signs will be captured during tSCS for analysis and will be monitored continuously as per standard of care.

When available, clinically acquired MRI data and intraoperative MEPs obtained as part of standard care will be reviewed. MRI severity will be characterized using the Brain and Spinal Injury Center (BASIC) score and used as an exploratory descriptor of injury severity and natural recovery potential (Talbott et al., 2015; Dhall et al., 2018).

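### The Phase 2 efficacy RM-ANOVA labels change over trials an effect of stimulation, although that term pools active and sham, and it does not say which of its three terms decides efficacy.

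*Protocol article*

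**What the plan says.** In the section Analysis of primary and secondary efficacy outcome measures, the primary efficacy outcome is "change in ISNCSCI lower motor score over time for Phase 2". For this and all other repeated measures, the plan states that "we will use a factorial within-subjects repeated-measures analysis of variance (RM-ANOVA) to assess statistically significant change over time". Three effects are to be read from that model:

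1. the group main effect, worded as "the overall between-subjects effect of stimulation to determine the group differences between the stimulation and control groups";
2. the group-by-time term, worded as "the difference in changes over time between groups";
3. the term at issue here, worded as "the within-subjects effect of stimulation over trials, to determine the extent to which each individual changes over time".

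Table 1 (Outcomes) gives the primary efficacy outcome two descriptions, "Immediate change in scores with acute tSCS Change in scores from baseline to post tSCS", both tested by repeated-measures ANOVA.

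Other sections bear on the reading. Trial design fixes a parallel-group Phase 2 with 5 participants per arm. Intervention and comparator states that sham participants receive no current. Data collection methods recognises spontaneous improvement, since the MRI score is "used as an exploratory descriptor of injury severity and natural recovery potential". Sample size calls the efficacy analyses exploratory and intends them to supply effect sizes for later trials.

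**The concern.** Treatment in Phase 2 varies between participants, not within them. In a model with a sham arm, the within-subject term for trials is the time main effect averaged over both arms. Everything that moves sham scores in the first week or so after injury enters it: natural recovery, resolution of spinal shock, familiarity with a repeated examination. Calling it an effect of stimulation is an error in the text, not a detail left to an analysis plan.

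The text also makes it easy to rely on that term. The outcome and the stated purpose of the model are both worded as change over time, and none of the three effects is named as the one that decides efficacy. A significant time term could be reported as a stimulation effect that the sham arm shows equally. An effect size taken from it would carry natural recovery into the planning of the next trial.

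**Working it through.** **Inputs from the protocol.** 5 active and 5 sham (Trial design); 5 daily sessions (Intervention and comparator); alpha 0.05 (Sample size); the three model terms above.

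**Assumptions, not in the protocol.** Gaussian scores with SD 1 at each occasion; equal within-person correlation ρ of 0.5, 0.8 or 0.9; baseline plus 5 sessions, so k = 6 levels; recovery rising linearly to R (in SD) by the last session, identical in both arms.

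**Step 1. The plan's own figure.** The protocol gives no power for the 10-participant analysis. It gives an observed power of 0.97 for the motor score (eta squared 0.18) in a chronic-injury study of 60. With f² = 0.18/0.82 = 0.22, a noncentral F calculation gives 0.94 to 0.95 for one numerator degree of freedom. For two it gives 0.997, or 0.904 under another convention for the noncentrality. The degrees of freedom are not stated, so 0.97 can be neither confirmed nor called wrong. Nothing below depends on it.

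**Step 2. What term 3 estimates.** Let the sham mean at occasion j be m_j and the active mean m_j + d_j. With equal arms, the pooled mean is m_j + d_j/2. The time term tests whether this is constant over j. If d_j = 0 throughout, it still rejects whenever m_j changes.

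**Step 3. How often it rejects with no stimulation effect.** For six equally spaced times from 0 to 1, the squared deviations from the mean sum to 2 × (0.25 + 0.09 + 0.01) = 0.70. The noncentrality is λ = 10 × R² × 0.70/(1 − ρ) = 7R²/(1 − ρ), on 5 and 40 degrees of freedom.

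| Shared recovery R | λ at ρ = 0.5 / 0.8 / 0.9 | Time term p < 0.05 (simulated) |
|---|---|---|
| 0.25 SD | 0.9 / 2.2 / 4.4 | about 9% to 27% over this range of ρ |
| 0.5 SD | 3.5 / 8.75 / 17.5 | 24% / 53% / 88% |
| 1 SD | 14 / 35 / 70 | 78% / 99.6% / 100% |

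At 0.1 SD the figure is only 5–8%. A second simulation on the points scale (between-patient SD 8, within-patient SD 2, both assumed) gives 5%, 44%, 98% and 100% for shared recovery of 0, 2, 4 and 6 points. With within-patient SD 3 and 4 points it gives 72%.

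**Step 4. The other two terms.** In the same no-effect runs, the group main effect and the group-by-time term each reject in about 5% of trials whatever the shared recovery. The false-positive problem is therefore confined to term 3. Because no term is decisive, the chance that at least one of the three is significant also matters: 13–14% with no effect and no recovery, and 31–89% with 0.5 SD recovery.

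**Step 5. The group main effect.** If baseline is one of k levels, a true step effect D present at every later occasion is averaged to D(k − 1)/k. That is 5/6 of D for six levels and 1/2 for baseline and one post score. For D = 4 points this is 3.3 and 2.0; the points-scale simulation agrees (3.37 and 1.98). Power at 5 per arm for that effect:

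| Levels | Group main effect | Group-by-time | Baseline-adjusted difference |
|---|---|---|---|
| 6 | 9% | 52% | 66% |
| 2 | 6% | 50% | 45% |

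If instead the effect builds gradually from 0 to 4 points over six levels, group-by-time has 45% and the adjusted difference 31%. On the SD scale, with a gradual 0-to-1 SD effect, the pairs are 54% and 41% at ρ = 0.8, and 87% and 62% at ρ = 0.9.

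**The case against.** The strongest reply is that the plan already contains a sound arm comparison. Its second term, the difference between groups in change over time, is not inflated by shared recovery and, with baseline as a level, removes baseline differences. This stands. A reader might infer that the trial has no valid test of stimulation, or that its only arm comparison is the weakest available. The protocol does not support that: two of the three terms compare arms, and low power belongs to the group main effect, not to group-by-time.

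A reader might also infer that baseline is certainly averaged into the group effect. Table 1 implies it by assigning the ANOVA to "Change in scores from baseline to post tSCS", but the analysis section speaks only of five trials. If baseline is not a level, there is no dilution, but the group effect is then unadjusted for baseline under simple randomization of 10 people. Either way the cost is power or precision, not false efficacy.

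Nor do the figures show that baseline adjustment is always better. It wins for an immediate step over six levels and loses for a gradual effect at higher correlation.

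Loss of participants with a missed session is not a finding. The protocol continues data collection after permanent discontinuation, and handling of missing scores is commonly left to the analysis plan.

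Finally, efficacy is declared exploratory, baseline characteristics are to be considered in interpretation, and no rule declares success from term 3. This lowers the stakes. It does not correct the label, and the outcome is still called primary.

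**Conclusion.** The point holds in two parts. First, the third term is described wrongly: in this design it is change over time in both arms together and cannot isolate stimulation. Second, three terms are offered for the primary efficacy outcome and none is named as decisive.

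That the term mixes both arms follows from the design alone. The rejection rates in the working rest on assumed recovery, correlation and Gaussian scores. Scores near zero in the most severe injuries would fit that model poorly, and very small recovery would make the inflation slight. The direction is the same throughout: the more both arms recover, the more often the term is significant.

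The dilution of the group main effect is conditional on baseline being a level of the model. Given the exploratory status of efficacy, this is a correction of moderate severity, not one that must be made before the trial can proceed.

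**What to change.** Before any Phase 2 data are seen:

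- Name one active-minus-sham contrast in lower motor score as the primary efficacy estimate. Either the arm-by-time contrast with baseline as a level or a baseline-adjusted arm difference over the sessions would serve. The choice should follow whether an immediate or a gradual effect is expected.
- State whether baseline is a level of the model or a covariate.
- Relabel the third term as change over time, report it descriptively by arm, and state that it will be used neither as evidence of stimulation benefit nor as the effect size for a later trial.

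The cost is wording only, since baseline scores are already collected, plus one degree of freedom if baseline is a covariate.
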